### C3Link Plus Sequence of Personalized Strategies

A sequence of individual strategies will be provided by study CHWs to women who remain unscreened at the 9-month follow-up. Women will be considered unscreened if they do not initiate any screenings or complete only one of the recommended screenings (breast or cervical). First, at 9 months, one-on-one education to reinforce concepts from group sessions and address specific misconceptions or myths expressed by the women. Second, those who remain unscreened at 10 months will receive motivational interviewing. Third, those who remain unscreened at 11 months will receive navigation to address any remaining barriers.

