### Data Collection

To assess the impact of the C3Link Core and Plus strategies on the mediating outcomes, we will conduct surveys to collect data from women, support persons, and providers in the clinics. Study CHWs will document strategy implementation in the C3Link CHW tracking tool, and this information will be used to determine the “dose of the intervention” (ie, in the community setting, dose is the number of education sessions attended or the type of individual-level intervention). We will track all health care service use of women enrolled in this study by conducting clinic audits at all 9 clinics and referral facilities. Data will be collected using tablets, which will contain REDCap (Research Electronic Data Capture; Vanderbilt University) programs to collect and store the data. Deidentified data will be transferred and stored in secure, password-protected servers. Research Triangle Institute (RTI) and Implenomics staff will conduct further data quality review, produce reports, and develop analytic files for collaborative analysis. Tables2  3 present end point definitions and biological, imaging, self-report, and clinic audit data collected at baseline and to be collected at 12-, 24-, and 36-month follow-ups.

**Table 2. T2:** Data collection at baseline, 12 months, 24 months, and 36 months. Data elements for primary, secondary, and follow-up end points—cancer care continuum.

Constructs or measures	Instrument and specification	Source	Timing
Proportion of women undergoing recommended cancer screening (primary end point measured at 24 months)	Cervical: Papanicolaou test (cytology laboratory), HPV^a^ DNA (Roche Cobas platform or Cepheid GeneXpert); breast: CBE^b^ or mammograms	Biological, imaging, and clinical procedures identified through clinic audits and this study’s database	12, 24, and 36 months
Proportion completing supplemental and diagnostic procedures in ≤90 days	Measured as days from referral to undergo procedures such as ultrasound, biopsy, colposcopy, and ablation of cervical lesions	Biological, imaging, and clinical procedures identified through clinic audits and this study’s database	24 and 36 months
Proportion of patients with cancer diagnosis initiating treatment in ≤90 days	Measured as days from cancer diagnosis to start of treatment; prespecified abstraction tool to identify dates and procedures	Biological, imaging, and clinical procedures identified through clinic audits and this study’s database	24 and 36 months

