### Data Analysis

Hypothesis testing will be carried out by intent to treat, and we will examine the effects at the individual level across the 3 randomization groups. We will use generalized estimating equation models to estimate the effects of the randomization groups. If the Hausman assumption of correlation between the random and fixed effects is violated, then we will include fixed effects representing cluster identification [71]. We will adjust for baseline covariates, including sociodemographic and behavioral factors, should the initial descriptive analyses suggest differences in the distribution of these factors across study randomization groups. We will also explore the use of propensity scores to control for systematic differences between the groups. In further analyses, we will compare differences in mediating outcomes across the groups and examine the potential moderating roles of key individual behavioral, social, and structural factors hypothesized to influence cancer screening and adherence along the cancer care continuum, as shown in Figure 1. We will test the “dose” of the C3Link Core and Plus strategies received as a covariate in these models. We will explore differences in breast and cervical cancer screening completion and report the proportion that complete at least one of the screenings. As appropriate, we will perform analyses separately or pooled together for the younger and older cohorts of women to assess whether care-seeking behavior differs by age group. A key aspect of interest in this study is the extent to which perceived and anticipated stigma affects care-seeking behavior and screening completion. In subsequent analyses, we will consider both medium-term outcomes within the first 12 months after enrollment and changes at any point during the 24-month and 36-month follow-up period to assess longer-term outcomes. To understand potential variation across communities, we will conduct comparisons to analyze differences in mediating and screening outcomes among each of the C3Link Core and Plus communities. We will also report on the overall quality of the screenings provided, women’s preferences for cervical cancer screening, and the type of procedures used along the continuum of care. For the C3Link Plus arm, we will document the increase in screening completion with each step in the series of individual strategies and the number of women requiring each type of strategy.

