Although cluster randomization reduces contamination across study arms, it increases the risk that women in each arm may differ at baseline. This study’s sampling frame will allow us to assess baseline differences before randomization and adjust our sampling process with propensity score weighting methods. Second, data could be missing because of nonresponse and study attrition. This study’s CHWs in each community will maintain regular contact with the women, and we will also use rigorous field data collection practices, including training data collectors, developing protocols, and monitoring fidelity continually. To limit missing data, we will train clinic staff and data collectors and implement continuous quality review. Furthermore, we will address any missing data by including demographic covariates that will serve as proxies for dropout and conducting sensitivity analyses.

We will select 1 eligible woman from within each household in the selected communities. To reduce interviewer bias, we will use the Kish method to provide a random and consistent procedure for women’s selection.

A key constraint in implementing strategies in low- and middle-income countries is funding. This is the first cancer screening study in Kenya, and to our knowledge, in any other limited-resource setting, that will evaluate implementation strategies in a predetermined sequence and assess effectiveness and cost at each step. This will allow us to determine the incremental cost-effectiveness of each strategy in the sequence to guide policy. For example, given the available resources and cost-effectiveness profile, a Kenyan county may decide to implement C3Link Core with only the first level in the sequence of C3Link Plus. Importantly, the findings will guide future studies in testing additional combinations and sequences.

This trial features novel evidence-based strategies to increase uptake of breast and cervical cancer screening in variously resourced settings in a cost-effective process. We anticipate that the findings will be valuable not only in Kenya but also in other sub-Saharan African countries.

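### In the Plus arm the individual-strategy dose depends on still being unscreened, so using it as a covariate for screening, or crediting each step with the screens that follow, gives biased secondary results

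*Protocol article*

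**What the plan says.** Under Data Collection, the article defines dose in the community setting: "dose is the number of education sessions attended or the type of individual-level intervention". Under Data Analysis, after the intent-to-treat paragraph and within the further analyses, it plans to test the dose "of the C3Link Core and Plus strategies received as a covariate in these models".

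The section C3Link Plus Sequence of Personalized Strategies sets who receives each step. It begins at month 9: "A sequence of individual strategies will be provided by study CHWs to women who remain unscreened at the 9-month follow-up". It defines the trigger: "Women will be considered unscreened if they do not initiate any screenings or complete only one of the recommended screenings". It then escalates: "those who remain unscreened at 10 months will receive motivational interviewing", and "those who remain unscreened at 11 months will receive navigation to address any remaining barriers". Table 1 gives the same three time points.

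For the Plus arm, Data Analysis adds that "we will document the increase in screening completion with each step in the series of individual strategies". The Discussion (Defining Features of our Approach) builds on evaluating effectiveness and cost at each step: "This will allow us to determine the incremental cost-effectiveness of each strategy in the sequence to guide policy". Its example is a county that adopts Core with only the first Plus level. The abstract's conclusions also promise incremental cost-effectiveness for each strategy.

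**The concern.** There are two separate faults.

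**Dose as a covariate.** A Plus woman moves up a level only while she has not completed both screenings, which is the complement of the outcome. If the steps are delivered as planned, she stops at level 0, 1 or 2 because she was screened. A model of screening completion that contains this dose has a consequence of the outcome on its right-hand side. Low dose will go with success and high dose with failure, whatever the strategies do. A useful strategy can look harmful, and the Plus coefficient is inflated to compensate.

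**Step-by-step crediting.** Some women unscreened at month 9 would have been screened later anyway. Counting screens after each step in Plus alone assigns this background uptake to whichever step was open. This is uncontrolled attribution in a group selected for being unscreened, and later steps also act on a more resistant group.

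The incremental effect and cost-effectiveness of each strategy are at stake. The article presents them as the study's novelty and as guidance for county policy.

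**Working it through.** The article states no figure for dose or step effects, so there is none to reproduce. The question is what the planned analyses return when the individual strategies have no effect.

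**Inputs.** From the article: 30% uptake in Core at 24 months (Study Design and Sample Size Determination), and steps at months 9, 10 and 11. Assumed: a constant screening rate, full delivery of the steps, a 0 to 3 dose score, a linear model, and Plus also at 30% (no step effect).

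**Proportion still unscreened.** Monthly rate h = -ln(0.70)/24 = 0.01486, and S(t) = exp(-ht):

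- S(9) = 0.8748
- S(10) = 0.8619
- S(11) = 0.8492
- S(12) = 0.8367
- S(24) = 0.7000

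**Step crediting under no effect, in points of all Plus women.**

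| Step | Window (months) | Credited |
|---|---|---|
| One-on-one education | 9 to 10 | 87.48 - 86.19 = 1.29 |
| Motivational interviewing | 10 to 11 | 86.19 - 84.92 = 1.27 |
| Navigation | 11 to 24 | 84.92 - 70.00 = 14.92 |
| Navigation | 11 to 12 | 84.92 - 83.67 = 1.25 |

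In a simulation of 400,000 women, Plus showed 1.3, 1.3 and 15.0 per 100 and Core showed 1.3, 1.3 and 14.9 in the same windows, although Core women receive no steps.

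**Dose in the screening model under no effect.** In Plus, 12.5% of women have dose 0, 1.3% dose 1, 1.3% dose 2 and 84.9% dose 3. Completion is 100% at doses 0, 1 and 2, and 14.92/84.92 = 17.6% at dose 3. Individual-strategy dose is zero throughout Core, so in a linear model with arm and dose the dose slope comes from Plus alone:

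- E(D) = 0.8748 + 0.8619 + 0.8492 = 2.586
- E(D²) = 0.8748 + 3(0.8619) + 5(0.8492) = 7.706
- Var(D) = 7.706 - 2.586² = 1.020
- E(YD) = 0.0129 + 2(0.0127) + 3(0.1492) = 0.486
- Cov(Y,D) = 0.486 - 0.30 × 2.586 = -0.290
- Dose slope = -0.290/1.020 = -0.284 per step (truth 0)
- Plus versus Core coefficient = 0.30 + 0.284 × 2.586 - 0.30 = about +0.73 (truth 0)

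The simulation gave -0.284 and +0.734. Its intent-to-treat difference, without dose, was -0.001.

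**When the steps work, or women differ in readiness.** Simulated with and without a frailty of variance 1:

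| Hazard ratio after month 9 | Intent-to-treat difference | Dose slope | Dose slope with frailty |
|---|---|---|---|
| 1 | -0.001 | -0.28 | -0.30 |
| 2 | +0.14 | -0.24 | -0.27 |
| 3 | +0.25 | -0.20 | -0.25 |

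**Dilution by incomplete delivery.** Suppose 20% of Plus women, unrelated to their screening, receive no step. (The 20% borrows the article's attrition allowance for scale only.) Then E(D) = 0.8 × 2.586 = 2.069, E(D²) = 0.8 × 7.706 = 6.165, Var(D) = 1.886, and Cov(Y,D) = 0.8 × 0.486 - 0.30 × 2.069 = -0.232. The slope is -0.232/1.886 = -0.12 and the Plus coefficient 0.12 × 2.069 = about +0.25. Both are smaller and still wrong.

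**Check of the remedy.** Among women unscreened at month 9, the no-effect case gives (87.48 - 70.00)/87.48 = 20.0% screened by month 24 in each arm. That is the correct null.

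**The case against.** Hypothesis testing is by intent to treat. Dose appears only among the further analyses, and the models it would enter are most naturally those for mediators and moderators. A reader might infer that the main arm effect will be adjusted for dose and so destroyed. The text does not plan that, and this part of the objection stands. Where the dependent variable is self-efficacy, stigma or social support, dose is not a function of the outcome by construction.

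Dose also includes group sessions attended, in both Core and Plus. Attendance is self-selected after randomisation and therefore confounded, but nothing in the text makes it depend on being unscreened. The exact argument covers only the individual-strategy part.

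The 100% completion at doses 0 to 2 assumes full delivery and no loss. The article allows for up to 20% attrition and will measure fidelity, so the coefficients above sit at the strong end. The linear score is also an assumption, because the article speaks of the type of strategy and of generalized estimating equations.

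A reader might infer that navigation would look about 11 or 12 times as effective as each earlier step. That needs the last window to run to month 24, which the article does not state. With one-month windows the three credits are nearly equal.

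Finally, counts per step are plain description, and the stated short-term cost-effectiveness objective compares trial arms. That holds for the counts. It does not cover the Discussion and abstract, which promise incremental cost-effectiveness for each strategy. Nor is this a detail left to the analysis plan: the article itself names the covariate and the step-level inference.

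**Conclusion.** The concern holds for secondary analyses and does not threaten the primary end point.

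With screening completion as the outcome, the individual-strategy dose in Plus is largely a consequence of that outcome. Its coefficient is biased towards harm and the arm coefficient is distorted. With no true effect, these are about -0.28 per step and +0.73, given a constant rate, full delivery and a linear score. The dose slope was negative in every simulated scenario, including those where the steps doubled or tripled the screening rate. Refusals and attrition reduce the size.

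The step-by-step increases in Plus alone cannot support effectiveness or cost-effectiveness per strategy, because uptake that would have occurred anyway is credited to the steps: about 1.3, 1.3 and either 14.9 or 1.25 points, depending on an unstated final window.

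**What to change.** 1. State that dose is excluded from every model that estimates arm effects on screening, and name the models in which it will be tested.
2. Estimate the add-on effect as Plus versus Core, by randomised arm, among women unscreened at month 9. The two arms are planned alike until then, so the comparison is protected if delivery follows the plan.
3. State the window for each step. Base step-level effectiveness and cost-effectiveness on Plus minus Core differences in those windows.
4. Label the comparisons for the second and third steps non-randomised, or analyse them with a method for time-varying treatment. Once the first step has acted, the women still unscreened in the two arms need not be alike.
5. Keep raw counts per step as description.

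This changes only wording and analysis, since clinic audits already track enrolled women's service use. It can be settled before the 24-month analysis planned for early 2027. The cost is smaller and less precise step estimates, and a more cautious claim for the later steps.

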### Assessing Multilevel Implementation Outcomes Using a Mixed Methods Approach

The objective of this assessment is to seek feedback from those implementing and receiving the strategies to evaluate the process of implementation. Data collection for this assessment will take place at 12 months post start of the intervention. We hypothesize that the C3Link Plus package of strategies will be more complex to implement in the community setting than the C3Link Core; therefore, we will compare the implementation outcomes between these 2 study arms to inform the selection of combination strategies. We will collect feedback from stakeholders across the 18 C3Link Core and Plus communities using a set of qualitative measures. The explanatory sequential design will strengthen the validity of quantitative data through triangulation and support the development of rich conclusions and actionable policies.

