**Methods:**

We will create the C3Link package aimed at increasing breast and cervical cancer screenings, and adopt a study design to assess and evaluate sustainability in 3 counties: Machakos, Nakuru, and Nyeri. Three noncontiguous communities for each of the 9 study clinics (3 per county) will be randomly assigned to one of the study arms using the R (R Foundation) program. The intensity of the strategies varies from low (awareness campaign for the enhanced usual care arm), to medium (C3Link Core arm with study community health worker–led group education and study community health worker–embedded clinic teams enhanced with practice facilitation), and to high (C3Link Plus arm with C3Link Core and a predetermined sequence of individual strategies). Women aged 30 to 55 years (1 per household) will be eligible to participate and could select a support person for inclusion. Trained data collectors will conduct surveys for women, their support persons, and from providers in the clinics using questionnaires, tracking tools, and focus group discussion guides. We will collect data and conduct interviews and focus groups to identify underlying moderating factors associated with the successful implementation of strategies. We will use implementation science methods to evaluate the effectiveness, implementation outcomes, and cost-effectiveness of the C3Link program compared with the enhanced usual care.

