The theoretical framework used, based on the socioecological model [32], is presented in Figure 1. Drawing on the literature and prior studies already cited, we will create the C3Link (cancer community–clinic linkage) multicomponent strategies targeted at barriers at the individual, interpersonal, and structural levels. These strategies are guided by the COM-B (Capability, Opportunity, and Motivation–Behavior) change model [3], in which capacity (CHW-facilitated cancer knowledge and risk assessment), opportunity (availability of high-quality screenings and confidence in the health care system), and motivation (self-efficacy, peer support, and care-seeking behavior) [4,6,7,12-16,26,33-35] interact to facilitate behavior change. Given the extremely low levels of cancer screening in Kenya and the importance of screening to reduce premature mortality, community stakeholders deemed it unethical to use the “current standard of care” as the comparison arm. We will, therefore, vary the intensity of the strategies from low (awareness campaign for the enhanced standard of care), to medium (C3Link Core with CHW-led group education and CHW-embedded clinic teams enhanced with practice facilitation), and to high (C3Link Plus with C3Link Core and a predetermined sequence of individual strategies). We will test the hypothesis that the C3Link (Core or Plus) combination of CHW-led community strategies for women (individual level) and their families (interpersonal level), along with health system practice facilitation (structural level), will increase cancer screening compared to the enhanced standard of care. Furthermore, we anticipate that CLink Plus will improve screening outcomes the most but will also require the most resources. Assessment of implementation outcomes, using the Proctor framework [36] and incremental cost-effectiveness analysis, will guide the selection of optimal strategies.

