Preimplementation phase for planning (6 months)		
Community—train CHWs^b^	13 basic modules plus 6 modules of study-specific content	No study CHWs
Clinic—strengthen quality, referrals, and provider interactions	Readiness assessment; standard procedures, diagnosis triage; training on high-quality screening and documentation	Readiness assessment; standard procedures, diagnosis triage; training on high-quality screening and documentation
Intervention phase to test multicomponent strategies (24 months implementation and follow-up)		
Community— Increase women’s knowledge, self-efficacy, care-seeking behavior, and social support (reduce stigma) Deliver individual strategies that increase in intensity to women who need additional support (C3Link Plus only)	C3Link CHW-led education sessions (each community): Three-weekly women’s club meetings with education modules Six group sessions for family members or support persons	Awareness campaign in the community using flyers developed and provided by the National Cancer Institute of Kenya
Community— Increase women’s knowledge, self-efficacy, care-seeking behavior, and social support (reduce stigma) Deliver individual strategies that increase in intensity to women who need additional support (C3Link Plus only)	C3Link Plus only—focus on care-seeking behavior: Level 1: women not screened at 9 months will receive one-on-one education, level 2: women not screened at 10 months will receive individual counseling through motivational interviewing, and level 3: women not screened at 11 months will receive navigation to address barriers	Awareness campaign in the community using flyers developed and provided by the National Cancer Institute of Kenya
Clinic— Embed study CHWs so that, with their support, results and referrals are conveyed Improve the quality of screening	Practice facilitation with community linkages (each clinic) Monthly case review meetings with study CHWs and PDSA^c^ cycles with clinic teams led by clinic champions	Those who visit clinics may benefit from improvements, but there are no community–clinic linkages with CHWs
Maintenance phase to test reduced level of support (additional 24 months for a total of 36 months of follow-up)		
Community—provide support to maintain behavior change	Quarterly women’s club meetings Two group sessions for family members or support persons	Awareness campaign continues

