### Recruitment

The 3 communities per study clinic will be randomly assigned to one of the following study arms: C3Link Core, C3Link Plus, or enhanced standard of care. Trained study data collectors and study CHWs will visit households in the selected communities with the help of county CHWs (promoters). They will visit households in selected communities and enroll eligible women. Women will be eligible to participate if they are 30 to 55 years of age to capture most cases of persistent HPV infections (lower age limit) and those within the peak age groups of breast cancer incidence rate in Kenya (higher age limit). These women will be due to receive both breast and cervical cancer screening during this study’s intervention phase based on Kenyan guideline recommendations, not experiencing breast or cervical cancer symptoms, not pregnant, fluent in a study language (English, Kiswahili, Kamba, Kalenjin, and Kikuyu), and have plans to remain in the community for at least 2 years. We will include women who meet the inclusion criteria (1 per household using the Kish method) [65].

The study CHWs will administer a short survey to all women to assess eligibility for this study. The data collectors will administer the baseline survey to women who will give voluntary informed consent to participate. Each enrolled woman will be allowed to select a support person (spouse or community member) older than 18 years of age—the legal age for consent for health research in Kenya, with help from their CHW if needed. Selecting a support person will be voluntary. Study CHWs will administer a support person eligibility checklist tool before data collectors administer the support person baseline survey to those who give voluntary informed consent.

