### Quantitative Measures

We will collect measures as outlined in Table 4 for both C3Link Core and C3Link Plus strategies.

**Table 4. T4:** Implementation outcomes measurement.

Constructs	Measures	Stakeholder and data	Frequency
Acceptability, feasibility, and appropriateness	AIM^a^, FIM^b^, and IAM^c^ 4-item measures	Women, family, study CHW, and clinic team surveys	24- and 36-month follow-up
Fidelity^d^ (group education, clinic team meetings, and individual strategies)	All content or topics are delivered, and sessions and meetings take place in the frequency and sequence planned	Study CHW tracking tool and clinic meeting minutes	12, 24, and 36 months
Sustainability	SMSS^e^ subscales specific to strategies	Study CHW and clinic team survey	24 and 36 months

a AIM: Acceptability of Intervention Measure.

b FIM: Feasibility of Intervention Measure.

c IAM: Intervention Appropriateness Measure.

d Dose is also included, and details are provided in Tables2  3.

e SMSS: Sustainment Measurement System Scale.

Our measurement will include the 4-item questions from each of the Acceptability of Intervention Measure, Feasibility of Intervention Measure, and Intervention Appropriateness Measure [72]. We will collect implementation feedback from C3Link CHWs and clinic teams participating in team meetings. The fidelity measures described in Table 4 will be compiled annually throughout this study’s implementation, and summary statistics will be generated to assess compliance with study protocols. Sustainability will be assessed using subscales of the Sustainment Measurement System Scale [73] applicable to the CLink package of strategies.

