### Qualitative Feedback

We plan to conduct interviews and focus groups to identify underlying moderating factors associated with the successful implementation of strategies, along with facilitators and barriers to inform future scale-up activities. First, at the end of the intervention implementation phase (24 months), trained data collectors will interview all 18 study CHWs from the C3Link Core and Plus communities and 6 clinic team members participating in C3Link implementation activities in each of the 9 clinics. These 18 CHWs are the total number of C3Link CHWs, where 9 are from the C3Link Core arm, and 9 are from the C3Link Plus arm. These CHWs will be distributed equally among the 3 counties—6 per county. We anticipate that differences and similarities will be based on study arm, county, or on the different iterations of the 2 variables. Categorization by study arm, by county, and by the different iterations may enrich the stories, but data saturation may be compromised. This may be reduced by the fact that participants will be information-rich, having been involved in the implementation continuously for over a year. We will develop an interview guide with questions and probes to seek feedback from study CHWs and clinical teams on their level of preparedness to implement the strategies, their assessment of the quality of the delivery, and the level of responsiveness of the target groups. We will also pose open-ended questions to determine what they felt were facilitators to deliver the strategies and potential barriers. In follow-up questions, we will explore suggestions to address the barriers.

Second, at the end of the maintenance phase (36 months), the research team will conduct 6 focus groups with C3Link CHWs and clinic teams that were interviewed (2 focus groups per county). These focus groups will explore topics related to the sustainability of the package of strategies, drawing on the findings from the Sustainment Measurement System Scale survey results. The focus group setting will allow for discussion among these key stakeholders and offer concrete feedback for future implementation in terms of best practices to further optimize the delivery of the strategies. To facilitate analysis, all interviews and focus groups will be transcribed and translated with supervision from the Kenya grant implementation team and stored in secure servers.

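### Every clinic serves all three arms, so clinic-sourced implementation scores cannot be attributed to Core or Plus, and the arm contrast does not identify the effect of practice facilitation

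*Protocol article*

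**What the plan says.** **Allocation.** The abstract states: "Three noncontiguous communities for each of the 9 study clinics (3 per county) will be randomly assigned to one of the study arms". Recruitment repeats it: "The 3 communities per study clinic will be randomly assigned to one of the following study arms". Under Qualitative Feedback, the interviewees include "6 clinic team members participating in C3Link implementation activities in each of the 9 clinics", so C3Link activity runs in all 9 clinics.

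**Implementation comparison.** The section on multilevel implementation outcomes expects Plus to be harder to deliver in the community than Core, and concludes: "therefore, we will compare the implementation outcomes between these 2 study arms to inform the selection of combination strategies". Quantitative Measures says the Table 4 measures are collected for both packages. Its source for acceptability, feasibility and appropriateness (AIM, FIM, IAM) is "Women, family, study CHW, and clinic team surveys". Sustainability (SMSS) comes from study CHWs and clinic teams. Fidelity comes from the CHW tracking tool and clinic meeting minutes.

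**Package hypothesis.** The Background hypothesises that CHW-led community strategies, "along with health system practice facilitation (structural level), will increase cancer screening compared to the enhanced standard of care". Table 1 places practice facilitation in the Core/Plus column. For the enhanced standard of care, the same row reads: "Those who visit clinics may benefit from improvements, but there are no community–clinic linkages with CHWs".

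**The concern.** A comparison between two arms needs outcomes that belong to one arm or the other. A clinic-team member who works with both the Core and the Plus community of a clinic belongs to neither, and the protocol gives no rule for placing that person's score. If clinic scores are pooled into both arms, the Core-versus-Plus difference shrinks towards zero by construction. If they are left out without saying so, the sustainability comparison rests on far fewer respondents than Table 4 suggests. This comparison is meant to guide which combination of strategies is selected.

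The package hypothesis has a related difficulty. It credits facilitation as part of what will outperform enhanced care, but facilitation is present in the clinics that control women use. A small arm difference could then be taken to mean that the whole package does little, when one part of it was never contrasted.

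**Working it through.** **Step 1. Do the arms share clinics?** Inputs are from the abstract, the sample size section and Qualitative Feedback.
- Communities: 9 clinics × 3 = 27; 27 / 3 arms = 9 per arm; 27 × 100 women = 2700, the stated total.
- Study CHWs: one per C3Link community, 9 Core + 9 Plus = 18; 18 / 3 counties = 6 per county, as stated.
- The Recruitment sentence, read alone, could mean that a clinic's three communities all go to one arm. That would give 9 / 3 = 3 clinics per arm and C3Link activity in only 6 clinics. The protocol says all 9 have it, so assignment is within clinic.
- Clinics belonging to a single arm: 0 of 9.

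**Step 2. Which Table 4 sources carry an arm?**

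| Construct | Arm-specific source | Shared source |
|---|---|---|
| Acceptability, feasibility, appropriateness | women, support persons, study CHWs | clinic team |
| Fidelity | tracking tool: group education, individual strategies | clinic meeting minutes |
| Sustainability | study CHWs (9 versus 9) | clinic team |

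Every row has a shared source. Every row also keeps an arm-specific one.

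**Step 3. How thin is 9 versus 9?** For scale only, take an unpaired two-sided t test at 5%: df = 9 + 9 − 2 = 16, noncentrality = d × √(9/2). At d = 1.45 SD the noncentrality is 1.45 × 2.121 = 3.08 and power is 82.3%. In steps of 0.05 SD from 1.00, this is the first to reach 80%. The protocol does not name a test for this outcome, and pairing by clinic could do better.

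**Step 4. What differs between C3Link and control?** Inputs are Table 1 and Implementation Strategies.

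| Component | Core/Plus | Control |
|---|---|---|
| Readiness assessment, procedures, screening training | yes | yes |
| Clinic quality improvement under facilitation | yes | women who attend may benefit |
| CHW linkage to the clinic | yes | no |
| CHW-led group education | yes | no (flyers) |
| Individual strategies | Plus only | no |

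The contrast with control is therefore community strategies plus CHW linkage. Clinic facilitation is common to all arms.

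**Step 5. Does this upset the stated power?** The plan's figure is over 80% for 15% versus 30%, with an intraclass correlation (ICC) of 0.03 to 0.05 and 20% attrition. Effective n per arm = 9 × 80 / (1 + 79 × ICC).
- ICC 0.03: 720 / 3.37 = 213.6, power 96.3%.
- ICC 0.05: 720 / 4.95 = 145.5, power 86.9%.

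The figure reproduces (normal approximation). If shared facilitation raised control uptake above 15% while C3Link stayed at 30%, power at ICC 0.03 / 0.05 would be 86.2% / 70.9% at 17.5% control uptake and 66.6% / 50.4% at 20%. These control rates are assumptions. The protocol gives no estimate of the spillover.

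**The case against.** The strongest reply is that the Core-versus-Plus comparison rests on complexity in the community setting, and the data for that are arm-specific: women, support persons, 18 study CHWs and the tracking tool. This stands. A reader might infer that the comparison as a whole cannot be made; the documents do not support that.

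Second, the text does not say that a clinic respondent gives one undifferentiated rating. Measures are said to be collected for both packages, and the SMSS subscales are described as specific to strategies. Separate ratings are therefore compatible with the text, but nothing commits to them, and no rule for assigning clinic data is given.

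Third, a reader might count the clinic interviews (6 × 9 = 54) and the provider survey as lost. They are not. Someone who works with both arms can describe how delivery differed, and no between-arm comparison is stated for the provider survey.

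Fourth, the hypothesis concerns the combined package, none of the four listed hypotheses isolates facilitation, and the exposure of control women is disclosed in Implementation Strategies and Table 1. The package remains testable against enhanced care, and CHW linkage does differ by arm. What remains is that the disclosure is not carried into the hypothesis or the conclusion.

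Fifth, a reader might infer that charging facilitation to Core and Plus overstates the cost per woman screened. The protocol states neither an allocation rule for shared clinic costs nor their share, so no such error can be shown.

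**Conclusion.** The point holds within limits. Clinic-team AIM/FIM/IAM and SMSS scores, and fidelity of the clinic meetings, have no arm in any of the 9 clinics, yet Table 4 lists them among the measures for the planned comparison. Without a rule for them, sustainability comes down to 9 versus 9 study CHWs. The other constructs keep usable arm-specific data. The contrast with control estimates community strategies and CHW linkage added to shared clinic facilitation; the effect of facilitation itself is not identified.

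This rests on reading the allocation as one community per arm in each clinic. The counts support that reading, but Figure 2 could not be seen. The randomisation, the primary end point and the intent-to-treat comparison are not invalidated. The dilution figures show sensitivity and are not evidence that the trial is underpowered. This is a cheap, worthwhile improvement to secondary outcomes and to the wording of the main claim.

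**What to change.** 1. Before the 24-month round, have each clinic respondent rate the Core linkage and the Plus linkage separately, and analyse the difference within respondent. Alternatively, limit the Core-versus-Plus comparison to women, support persons, study CHWs and community fidelity data, and report clinic measures descriptively for the 9 clinics. Table 4 places the clinic-team surveys at 24 and 36 months, and 24-month collection is due in early 2027. Separate ratings not asked for then cannot be recovered later.
2. Restate the hypothesis and conclusion as the effect of community strategies and CHW linkage added to clinic facilitation available in all arms.
3. State in the economic plan how shared clinic costs are allocated across arms. This is a point of clarity only.

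The cost is a few duplicated survey items and a narrower claim about the package. Randomisation and sample size do not change.
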